#### 3.5.1. Power sample calculation

For sample and power calculations, this study is powered based on changes in total body fat assessed by DXA. Considering a type I error of 5% and a power of 95% to detect differences at the dependent variable, with a statistical significance and an effect size of 0.93 (differences in FM (kg) were considered following Byrne et al. results [6]), a total of 26 participants per group will be needed (using GPower software version 3.1.9.6). Considering a 30% drop-out rate [6] throughout the study, we will recruit 74 participants (37 in each group).

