## 2. Methods

### 2.1. Study design

The BREAK study is a RCT (allocation ratio of 1:1) that will be performed in adult women with obesity, randomly divided in 2 parallel groups: 1) CER and 2) IER. This study will include a three-phase intervention:

2 weeks of neutral EB;Active WL phase, where both groups will undergo 16 weeks of ER: CER—16 weeks of continuous ER; IER—2 weeks of ER interspersed with 1 week in EB, leading to a total of 23 weeks. IER length is 7-week longer than CER due to the 7x1-week of neutral EB, to maintain the same magnitude of ER in both interventions;8 weeks in neutral EB.

Participants will also be evaluated 12 months after the 3rd phase, to determine WL maintenance success. SPIRIT diagram is presented in Fig 1.

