### 3.5. Statistics

Statistical analysis will be performed using SPSS statistics software version 29.0, 2022 (SPSS Inc., an IBM Company, Chicago IL, USA), with a statistical significance set at p<0.05 (2-tailed).

Descriptive statistics will be calculated (mean, standard deviation, and range). Linear mixed models will be used to assess outcomes for the impact of group, time and group*time interaction, including the randomized group (control vs intervention group) and time (baseline at the 2-week EB, at the start and every 4-week of ER intervention phase, at the start and at the end of the 8-week post-diet EB phase, and at the end of WM phase) as fixed effects. When necessary, adjustments for confounding variables (covariates) will be considered. The covariance matrix for repeated measures within subjects over time will be modelled as unstructured or, if necessary, compound symmetry. The normality of model residual distributions will be examined graphically and with the Kolmogorov-Smirnov test. Difference-in-differences between IER and CER throughout time will be assessed by performing contrasts [Difference-in-differences (DiD)], calculated as the difference between changes for IER (Difference_IER = T2 -T1) and changes for CER (Difference_CER = Time2 –Time1): DiD = (Difference_IER)–(Difference_CER).

All analysis will be intention-to-treat, including data from all the participants who will assign in this study. Sensitivity analyses will be carried out for some variables of interest, by using single imputation of missing data to predict missing outcomes from demographics and baseline measures.

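### The stated 95% power does not fit 26 per group under the two-tailed test: a two-sample comparison at effect size 0.93 has about 91%

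*Protocol article*

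**What the plan says.** Section 3.5.1 (Power sample calculation) names the outcome: "this study is powered based on changes in total body fat assessed by DXA". It then sets the error rates, "Considering a type I error of 5% and a power of 95% to detect differences at the dependent variable", with "an effect size of 0.93 (differences in FM (kg) were considered following Byrne et al. results [6" as the standardised difference. The result is that "a total of 26 participants per group will be needed (using GPower software version 3.1.9.6". A 30% drop-out allowance takes this to 37 per group, 74 in all. The paragraph does not state the number of tails.

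Section 3.5 (Statistics) does state it for the analysis: "with a statistical significance set at p<0.05 (2-tailed". Section 2.1 gives equal allocation to two parallel groups. Nowhere does the article plan a one-sided test.

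The Abstract lists change in fat mass as a primary outcome, so this calculation supports a primary comparison. It is also the only justification given for 74 participants.

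**The concern.** The paragraph prints a complete set of inputs and a result, so it can be checked without any outside source. Under the two-tailed test that section 3.5 declares, an effect size of 0.93 with 26 per group gives less than 95% power.

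What is at stake is how the fat-mass result will be read. If the comparison is null, readers will weigh it against a stated 5% chance of missing the planned difference. On the plan's own figures that chance is about 9%.

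**Working it through.** **Inputs.** Effect size d = 0.93, type I error 5%, power 95%, 26 per group (section 3.5.1); two-tailed (section 3.5); 1:1 allocation (section 2.1). I read 0.93 as a difference in mean change divided by its standard deviation, and treat the between-group contrast of changes as a two-sample t-test.

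**Formula.** With n per group, df = 2n − 2 and the noncentrality parameter is d × √(n/2). Power is the probability that the noncentral t statistic falls beyond the critical value: t(0.95, df) for one tail, ±t(0.975, df) for two.

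**Reproducing 26.** At n = 26, df = 50 and the noncentrality is 0.93 × √13 = 3.353.

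| Test at 5% | n per group | Critical t | Power |
|---|---|---|---|
| One-tailed | 25 | 1.677 | 94.5% |
| One-tailed | 26 | 1.676 | 95.2% |
| Two-tailed | 25 | 2.011 | 89.6% |
| Two-tailed | 26 | 2.009 | 90.8% |
| Two-tailed | 31 | 2.000 | 94.97% |
| Two-tailed | 32 | 1.999 | 95.6% |

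So 26 is the smallest n for 95% power with one tail. It is also the smallest n for 90% power with two tails. It is not the smallest n for 95% power with two tails; that is 32.

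**Second method.** The normal approximation n = 2(z₁ + z₂)²/d² gives:

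- one-tailed, 95%: 2 × (1.645 + 1.645)²/0.93² = 25.03, rounded up to 26;
- two-tailed, 95%: 2 × (1.960 + 1.645)²/0.93² = 30.05, rounded up to 31.

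Its two-sided power at 26 per group is 91.8%. The conclusion does not depend on the method.

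**Could rounding of the effect size explain the gap?** No. Across 0.925 to 0.935, two-sided power at 26 per group runs only from 90.5% to 91.1%. Two-sided 95% power at 26 per group would need d of about 1.02.

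**Drop-out step.** 26/0.70 = 37.1, printed as 37. Expected completers are 37 × 0.70 = 25.9 per group. Putting 25.9 into the same formula gives 90.7% two-sided power, which does not differ in practice from 90.8%.

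**The case against.** **The cause is not known.** A reader might infer that the software was run with one tail selected, since that setting returns 26 from the printed 5%, 95% and 0.93. The article does not support stating this as fact. Section 3.5.1 is silent on tails, and a printed 95% that should have been 90% explains 26 equally well under the two-tailed test. In that case the sample size suits the planned test and a single number is wrong. This objection stands against naming a cause. It leaves the inconsistency in place, because under either explanation the stated 95% does not hold for the declared test.

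**The planned analysis is not a t-test on completers.** Section 3.5 specifies linear mixed models by intention to treat, with possible covariate adjustment. The 30% loss is assumed over the whole study, so a contrast at the end of energy restriction may have more than 26 women per group. With all 37 per group, two-sided power would be 97.6%. This stands as a qualification: about 91% belongs to a two-sample comparison of 26 completers per group. It does not restore the 95%, because section 3.5.1 ties that figure to 26 per group and claims no gain from repeated measures or covariates. The article also gives no within-person correlation and no drop-out by phase from which such a gain could be computed.

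**The trial is not thereby too small.** A reader might infer that recruitment should rise to 46 per group (32/0.70 = 45.7), or 92 in all. That follows only if 95% is kept as a firm target. Nothing in the article makes 95% indispensable, and power above 90% at the assumed effect is high.

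**The drop-out arithmetic is not an error.** A reader might also object that 37.1 should be rounded up to 38. Against an approximate 30% planning rate this is ordinary rounding, and it costs about 0.1 percentage points of power.

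**Conclusion.** The power statement is wrong as written. A 5% type I error, 95% power, an effect size of 0.93 and 26 per group cannot all hold under two-tailed testing. With 26 evaluable per group the two-sided power is about 91%, an overstatement of roughly four percentage points, and the type II error is about 9% instead of 5%. Two-sided 95% power needs 32 evaluable per group.

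This rests on reading 0.93 as a standardised mean difference and on a two-sample comparison of change among completers. The power of the mixed model may differ and cannot be computed from the article. The error affects a stated property of the design. The trial's conduct, planned analysis and validity are untouched.

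**What to change.** Keep 74 participants. In section 3.5.1, state the number of tails and replace the power figure, for example: *with 26 evaluable women per group, an effect size of 0.93 and a two-sided 5% level, a two-sample comparison of change in fat mass has about 91% power.* If useful, add that 95% power would need 32 evaluable per group. The authors should check their saved software settings to see whether the tails or the printed power went wrong, and record which it was.

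The cost is one corrected sentence and a slightly less favourable power figure. No extra participants and no change to the analysis are needed, and the 37 per group can stand.

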**Methods:**

Seventy-four women with obesity and inactive (20–45 y) will be randomized to 16 weeks of CER or IER (8x2 weeks of energy restriction interspersed with 7x1 week in energy balance). Both groups will start with 2 weeks in energy balance before energy restriction, followed by 16 weeks in energy restriction, then 8 weeks in energy balance and finally a 12-month weight maintenance phase. Primary outcomes are changes in fat-mass and adaptive thermogenesis after weight loss and weight maintenance. Secondary outcomes include weight loss, fat-free mass preservation, alterations in energy expenditure components, and changes in hormones (thyroid function, insulin, leptin, and cortisol).

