Campbell et al. [23] investigated body composition changes in lean resistance trained individuals following a ~25% ER for 7 weeks in conjunction with 4-days/week resistance training, randomized to either IER or CER. IER cycled 5 days of ER with 2 days of EB using carbohydrate refeeds. The authors found that a 2-day carbohydrate refeed preserved FFM, dry FFM and REE during ER, compared to CER in resistance trained individuals. Davoodi et al. [30] compared IER and CER in 74 women with overweight and obesity for a six-week period. IER consisted of 3 cycles of 2 weeks (6-week total), and each cycle included 11 days of ER followed by 3 days of EB. IER was associated with a greater improvement in anthropometric measures, showed a better adherence to the dietary plan and a higher REE by the end of ER period, compared to CER. Byrne at al. [6] examined whether IER improved WL efficiency compared to CER in 51 men with obesity, for a 16-week ER period. IER group cycled 14 days of ER followed by 14 days of EB (30 weeks in total), with an ER of 33% in both IER and CER groups. The authors found a greater WL and fat loss with IER, and reported AT only for the CER group (~209 kJ/d) after a weight loss of ~8,4% of the initial weight, despite a greater weight loss in the IER group ~12,9%. As only men were included in the Byrne et al. study [6], there is a need to study the effects of a similar intervention in women. Furthermore, considering that the compensatory metabolic responses following ER and WL need a period of 7-to-14-days post-WL to be reversed [6, 25], and in order to maximize the ER/EB days´ ratio, another IER pattern should be considered. To our knowledge, this will be the first RCT comparing CER with IER (cycling 14 days of ER followed by 7-day EB periods), in women with obesity.

Pending this approach as a potential opportunity for obesity’s treatment, this paper describes the protocol for a RCT, targeting to evaluate the effects of an IER, interspersing 14 days of ER with 7 days of EB, comparing to a CER. The primary aim of the trial is to assess whether IER will determine a greater FM loss and a reduced AT during WL and after 12-month maintenance, avoiding weight regain, compared to CER, in women with obesity and inactive. Secondary outcomes include WL, retention of FFM, alterations in EE components, and AT plasma-derived indices (thyroid function, insulin, leptin and cortisol).

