#### 2.8.2. Rewards for participation

Participants will not receive any type of financial incentive. Nevertheless, they will benefit from a free nutritional intervention for WL and WM, which includes 8 nutrition appointments and weekly remote follow-up by a certified clinical dietitian for 78 weeks (CER group), or 85 weeks (IER group).

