The BREAK Study focuses not only in reducing energy intake through portion control, but also in improving nutritional quality of the diet, by increasing fruit and vegetable intake, and decreasing processed and energy-dense foods. Participants will be educated and encouraged to daily monitor their behavior, weight, and eating pattern, leading to self-efficacy for diet and WM, which are determinants of WL maintenance [66]. Although maintaining high levels of PA has been pointed out as a determinant of WL maintenance [74], the BREAK Study is a diet-only [75] intervention. Therefore, no PA recommendations will be given to participants throughout the WL and WM phases.

One of the strengths of The BREAK Study is the 2-week baseline EB for determining energy requirements, stabilizing weight, and adapting participants to the prescribed dietary plan. Another strength is the determination of REE and PA monitoring every 4 weeks of ER, allowing adjustment of the dietary plan to ensure the energy deficit of 33% during the 16-week ER phase. Monitoring AT-related hormone changes during WL and WM is also a strong point of this study, enabling a better understand of AT in both groups.

However, some limitations should be addressed, such as: i) the nutritional intervention occurs in a free-living scenario, with no food being delivered to participants, preventing a valid assurance that participants are in fact consuming the prescribed energy. To minimize this adherence limitation, participants are instructed to weekly share with the main investigator their overnight fasting body weight and photo records of their meals; ii) a large interindividual variability in PAEE is expected and may not be accurately detected by accelerometry; iii) the eventual more than expected drop out of the study, due to its length, possibly weakening the statistical power of the analysis.

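### The 30% drop-out allowance comes from a trial described only as 16 to 30 weeks long, so the stated power is not supported for the 12-month fat-mass outcome

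*Protocol article*

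**What the plan says.** - Section 3.5.1 (Power sample calculation) bases the size on change in total body fat by DXA: "Considering a type I error of 5% and a power of 95% to detect differences at the dependent variable", with "an effect size of 0.93" derived from the fat-mass results of reference 6. This gives 26 women per group. No time point is named.
- The same section then allows for losses: "Considering a 30% drop-out rate [6] throughout the study, we will recruit 74 participants (37 in each group". The rate, its source and the span it is meant to cover are all stated.
- The Introduction describes reference 6 as a trial in 51 men with a 16-week restriction period. Of its intermittent arm it says: "IER group cycled 14 days of ER followed by 14 days of EB (30 weeks in total". No longer follow-up is mentioned.
- Section 2.8.2 gives the length of the present trial: "for 78 weeks (CER group), or 85 weeks (IER group".
- The Abstract (Methods) states: "Primary outcomes are changes in fat-mass and adaptive thermogenesis after weight loss and weight maintenance". The primary aim in the Introduction also names the 12-month maintenance point.
- Section 3.5 sets the test "with a statistical significance set at p<0.05 (2-tailed") and plans linear mixed models over all visits.
- The Discussion lists as a limitation "the eventual more than expected drop out of the study, due to its length, possibly weakening the statistical power of the analysis". The sizing figure is not altered.

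**The concern.** The planned number rests on 26 evaluable women per group. The only support for reaching 26 is a drop-out proportion borrowed from a trial that, as described here, ran for less than half as long. Because the power statement names no time point, a reader will apply it to both primary fat-mass comparisons, the one after weight loss and the one after the maintenance year. If losses by 12 months exceed 30%, a null 12-month result would be read as stronger evidence of no difference than the trial can give.

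**Working it through.** **Inputs.** From section 3.5.1: effect size d = 0.93, type I error 5%, 26 per group needed, 37 per group recruited, 30% drop-out. From section 3.5: two-tailed test. From the Introduction: 16 and 30 weeks for reference 6. From section 2.8.2: 78 and 85 weeks here. The article gives no 12-month drop-out rate, so every rate other than 30% below is an assumption.

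**Method.** Two-sample t-test with n per arm: noncentrality d × √(n/2), degrees of freedom 2n − 2, power from the noncentral t distribution.

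**Step 1: reproduce the plan's figure.** With n = 26, the noncentrality is 0.93 × √13 = 3.35 on 50 degrees of freedom.
- One-sided 5%: power 95.2%, and 26 is the smallest n that reaches 95%. This is the printed result.
- Two-sided 5%, as section 3.5 requires: power 90.8%; 95% would need 32 per group.

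Drop-out: 26 / 0.70 = 37.1, and 37 × 0.70 = 25.9. The recruitment figure of 37 is consistent with 26 to within rounding.

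**Step 2: compare the periods.** 78 / 30 = 2.6 and 85 / 30 = 2.8. The 30% is applied to a period 2.6 to 2.8 times the longest duration the article gives for its source.

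**Step 3: power at 12 months by assumed drop-out** (37 randomised per arm, d = 0.93, completers only, equal loss in both arms).

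| Drop-out | Women per arm | Two-sided power | One-sided power |
|---|---|---|---|
| 30% | 25.9 | 90.7% | 95.1% |
| 40% | 22.2 | 85.7% | 92.0% |
| 50% | 18.5 | 78.5% | 87.0% |
| 60% | 14.8 | 68.5% | 79.5% |

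**Step 4: what would 30% over 30 weeks imply?** Assume that 30% was lost in 30 weeks. The weekly hazard is h = −ln(0.7)/30. Apply h up to the start of the maintenance year (week 33 IER, week 26 CER), then k × h for 52 weeks. Retention is exp[−h(33 + 52k)] for IER and exp[−h(26 + 52k)] for CER.
- k = 1: retention 0.364 and 0.396, or 13.5 and 14.6 women; two-sided power 66.0%.
- k = 0.5: 0.496 and 0.539, or 18.3 and 19.9 women; 79.9%.
- k = 0.25: 0.579 and 0.629, or 21.4 and 23.3 women; 85.9%.

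At the end of restriction (week 2 + 23 = 25 IER, week 2 + 16 = 18 CER) the same hazard leaves 0.743 and 0.807, with two-sided power 93.3%. The 30% allowance is therefore ample at that point.

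**Step 5: the reverse check.** For total loss at 78 to 85 weeks to be 30% at a constant rate, loss by week 30 would have to be 1 − 0.7^(30/78) = 12.8% or 1 − 0.7^(30/85) = 11.8%. That is less than half of 30%. It matters only if the source's 30% does refer to about 30 weeks, which the article does not say.

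**The case against.** The strongest reply is that the source's denominator is unknown. The 16 and 30 weeks are intervention lengths, and the article does not say how long reference 6 followed its participants or when the 30% accrued. If it covers a period like this trial's, nothing is lost. This stands: a reader might infer that power at 12 months has been shown to fail, or that some 60% of women will be lost, and the documents support neither.

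A reader might also infer that the plan assumes no losses in the maintenance year. It does not. The 30% is worded as a total over the whole study, and section 2.8.1 provides at least monthly phone or video contact in that year.

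The completers-only figures are somewhat pessimistic. Section 3.5 plans an intention-to-treat mixed model, and section 3 plans five DXA scans, so women who leave still contribute earlier data. This stands in part: earlier scans only partly replace a missing 12-month value, and the plan's own calculation also counts completers.

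The Discussion already discloses the risk, but it gives no figure and leaves section 3.5.1 unchanged. It also lists 12-month maintenance and body composition among the secondary objectives. The Abstract and the primary aim nevertheless make 12-month fat mass primary.

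Finally, the gap of about 4 points between 95% and 91% is a matter of one-sided against two-sided testing and should not be charged to drop-out.

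**Conclusion.** The point holds as a lack of support, not as a demonstrated shortfall. The article prints a drop-out rate, its source and its span, and its own description of the source does not cover that span. Measured against the two-sided 91% at 30% loss, the cost at 12 months would be about 5 points at 40% drop-out, 12 at 50% and 22 at 60%; it is zero if 30% is right.

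These figures assume d = 0.93, 37 randomised per arm, equal loss in both arms and completers only. Section 3.5.1 does not tie 0.93 to 12 months, so they show sensitivity to drop-out alone and do not forecast 12-month power. The 66% from a constant hazard needs the strong further assumption of 30% lost per 30 weeks throughout.

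It is also tempting to conclude that the printed 95% is sound at the end of restriction. It is not under the two-tailed test of section 3.5: 26 per group gives about 91%. The allowance for drop-out at that point is not in doubt.

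**What to change.** In section 3.5.1:

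1. Name the end of restriction as the time point of the power calculation, and restate its power for the two-tailed 5% test as about 91% with 26 per group at d = 0.93. Do not attach the printed 95% to it.
2. For the 12-month fat-mass change, do not carry over the printed power. Give power over a drop-out range labelled as an assumption: about 91% at 30%, 86% at 40%, 79% at 50% and 68% at 60% (completers only, two-sided, 37 per arm, d = 0.93).
3. Add that 0.93 is not tied to 12 months, and that the mixed model recovers some information from women who leave.
4. If the period over which reference 6 lost 30% is known, state it.

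This changes wording only. It needs no extra participants and leaves the design as it is. The one downside is a less favourable stated power.

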#### 3.5.2. Trial status

Recruitment for this clinical trial started on January 13^th^, 2022, and is expected to end on June 30^th^, 2024.

## 4. Discussion

This RCT aims primarily to evaluate the effects of an IER, interspersing 14 days of ER with 7 days of EB, on body composition (body weight, FM and FFM), and more specifically on AT, during WL and WM phase. It also aims to understand whether participants from both groups (IER and CER) will successfully maintain their WL 12 months after completion of the intervention.

Secondary objectives of this study are the following: (i) to compare the effects of IER and CER on WL, FM loss, and preservation of FFM and REE during the intervention phase; (ii) to determine which group is more successful in the 12-month WM phase and in improving body composition profile (higher FM loss with best preservation of FFM); (iii) to analyze if AT is maintained during WM phase; (iv) to analyze the impact of AT in WM phase, regarding the hormonal adaptation (plasma hormones: cortisol, insulin, leptin, thyroid free T3 and T4).

A 5% WL has been pointed out to be enough to improve metabolic parameters (glycemic measures and triglycerides, blood pressure, HDL and LDL cholesterol) and is currently a standard goal in WL interventions [65]. Nevertheless, a greater reduction of 10% or more can lead to maximal health benefits, reducing many of the comorbidities associated with obesity [66, 67]. In fact, according to Wing and Hill [68], successful WL maintainers should be defined as “individuals who have intentionally lost at least 10% of their body weight and kept if off at least 1 year”. With The BREAK Study we expect to find a clinically significant weight loss [69] of 10% in both groups, considering the length of the ER intervention, and the magnitude of ER [70].

According to Byrne and colleagues [6, 25, 71], adaptive responses to ER and WL can be reversed by a 7-to-14-day period of EB after, in adults with overweight or obesity. In “MATADOR” Study, a IER using a 2-week EB periods improved WL efficiency compared with CER, being AT only found in CER group, despite the lower WL and FM loss [6]. In review by Peos and colleagues [21], it was stated that “refeeds” with at least 7 days attenuate the adaptive responses to longer-term periods of ER, potentially by attenuating the reductions in EE. Furthermore, these authors also mentioned that adopting refeed periods in IER may provide a mental break from extended periods of ER, leading to a higher long-term adherence to the dietary plan compared to CER. Therefore, we also anticipate a major weight and FM loss in IER group, comparing to CER, with a greater retention of FFM, reducing therefore AT [6, 23, 30], due to the inclusion of 7-day breaks to restore EB every 2-weeks of ER, which can minimize the compensatory mechanisms associated with ER and WL, such as changes in appetite-related hormones [24] and some behavioral compensations such as increases in sedentary behavior [26].

During WL phase, we expect to find a reduction in all EE components, as usually seen during ER, namely REE and non-resting EE (spontaneous PA (SPA), non-exercise PA (NEPA), and exercise PA (EPA)) [72].

WL usually causes a reduction in thyroid hormones (T3 and T4), insulin and leptin, increasing appetite [7, 73], and causes an increase in cortisol, which reduces EE [22]. We expect to find a lower reduction in insulin, leptin, thyroid T3 and T4, as well as a lower increase in cortisol in IER, comparing to CER. The minimization of these compensatory adaptations can be explained by the 1-week EB every 2-weeks of ER. After ER intervention, we anticipate a successful WL maintenance in both groups, possibly greater in the IER group, as well as a lower AT.

The BREAK Study focuses not only in reducing energy intake through portion control, but also in improving nutritional quality of the diet, by increasing fruit and vegetable intake, and decreasing processed and energy-dense foods. Participants will be educated and encouraged to daily monitor their behavior, weight, and eating pattern, leading to self-efficacy for diet and WM, which are determinants of WL maintenance [66]. Although maintaining high levels of PA has been pointed out as a determinant of WL maintenance [74], the BREAK Study is a diet-only [75] intervention. Therefore, no PA recommendations will be given to participants throughout the WL and WM phases.

One of the strengths of The BREAK Study is the 2-week baseline EB for determining energy requirements, stabilizing weight, and adapting participants to the prescribed dietary plan. Another strength is the determination of REE and PA monitoring every 4 weeks of ER, allowing adjustment of the dietary plan to ensure the energy deficit of 33% during the 16-week ER phase. Monitoring AT-related hormone changes during WL and WM is also a strong point of this study, enabling a better understand of AT in both groups.

However, some limitations should be addressed, such as: i) the nutritional intervention occurs in a free-living scenario, with no food being delivered to participants, preventing a valid assurance that participants are in fact consuming the prescribed energy. To minimize this adherence limitation, participants are instructed to weekly share with the main investigator their overnight fasting body weight and photo records of their meals; ii) a large interindividual variability in PAEE is expected and may not be accurately detected by accelerometry; iii) the eventual more than expected drop out of the study, due to its length, possibly weakening the statistical power of the analysis.

We anticipate that The BREAK Study will allow us to better understand AT during WL and WM interventions in women with obesity. Moreover, we expect to find a successful alternative to CER, enabling more tailored nutritional interventions, according to individuals needs and lifestyle. This study will also allow participants to lose weight and FM, while attenuating AT, improving their metabolic health, and encouraging them to adhere to a healthy lifestyle and acquire nutritional knowledge that will facilitate WM in the long-term. Finally, the findings of this trial will enable evidence-based decisions for the treatment of obesity.
